## ***Abstract***

***Background:*** Adolescent alcohol use is a growing public health concern in Ethiopia. Theory-driven, peer-led educational interventions may modify psychosocial determinants of drinking behavior. This protocol describes a study designed to assess the effectiveness of a peer-led educational intervention grounded in the Theory of Planned Behavior (TPB) in changing alcohol-related intentions and self-reported alcohol consumption among secondary school students in Dessie and Kombolcha towns, Northeast Ethiopia.

***Methods:*** A quasi-experimental pretest-posttest control group design with class-level allocation will be conducted from February to June 2021 in four public secondary schools in Northeast Ethiopia. A total of 1,496 students aged 15–24 years will be assigned to intervention ( $n = 748$ ) or control ( $n = 748$ ) groups. Full randomization at the individual student level is not feasible due to the risk of contamination within classrooms, so intact classes will be used as units of allocation. The intervention consists of four weekly 60-minute peer-led sessions targeting TPB constructs and alcohol-related knowledge. Outcomes will be assessed at baseline and three months post-intervention using validated self-administered questionnaires. Primary outcomes are behavioral intention to consume alcohol and current alcohol use (past 30 days). Secondary outcomes include alcohol-related knowledge, attitudes, subjective norms, and perceived behavioral control. Generalized estimating equations (GEE) accounting for class-level clustering will be used to estimate adjusted effects.

***Discussion:*** This study will provide evidence on the effectiveness of a culturally adapted, peer-led, theory-based intervention to reduce alcohol use intentions and behaviors among secondary school students in Northeast Ethiopia. Findings may inform school-based prevention programs and policies in similar settings.

***Keywords:*** Alcohol use; adolescents; peer-led intervention; Theory of Planned Behavior; Ethiopia; school-based prevention; study protocol

# ***BACKGROUND***

## ***Global Burden of Adolescent Alcohol Use***

Alcohol consumption among adolescents represents a critical public health challenge worldwide. According to the World Health Organization's Global Status Report on Alcohol and Health (2018), approximately 26.5% of all adolescents aged 15-19 years globally are current drinkers [1]. The harmful use of alcohol during adolescence contributes to approximately 320,000 deaths annually among young people aged 15-29 years [2].

Adolescent alcohol use is associated with numerous adverse outcomes, including increased risk of injuries and accidents [3]; impaired brain development and cognitive function [4]; mental health disorders, including depression and anxiety [5]; risky sexual behaviors leading to unintended pregnancies and sexually transmitted infections [6]; poor academic performance and school dropout [7]; and increased likelihood of developing alcohol use disorders in adulthood [8].

## ***Alcohol Use in Ethiopia***

In Ethiopia, adolescent and youth alcohol use has emerged as a growing public health concern. Nationally representative data from the 2016 Ethiopian Demographic and Health Survey (EDHS) documented that among youth aged 15-24 years, 36.8% had consumed alcohol in the preceding month, 12.6% had chewed khat, and 0.95% had used tobacco [9]. These findings highlight the substantial burden of substance use among young Ethiopians and underscore the urgent need for effective prevention interventions.

A systematic review and meta-analysis by Ali and Worku (2020) estimated the prevalence of current alcohol consumption among school adolescents and youths in Ethiopia at 27%, with significant regional variation [10]. Regional studies have reported varying prevalence rates: Gondar preparatory schools at 31.2% [11], Nekemte secondary schools at 24.6% [12], Addis Ababa high schools at 28.3% [13], and Jimma secondary schools at 26.8% [14].

Key determinants of adolescent alcohol use in Ethiopia include peer pressure, parental drinking behavior, accessibility of alcohol, low perceived risk, and poor knowledge of alcohol-related harms [10–14]. The EDHS data further reveal that alcohol use among Ethiopian youth is more prevalent in urban areas and among those with lower educational attainment, highlighting the vulnerability of in-school and out-of-school youth populations [9].

## ***Theoretical Framework: Theory of Planned Behavior***

The Theory of Planned Behavior (TPB), developed by Icek Ajzen (1991), provides a robust framework for understanding and predicting health behaviors [15]. According to TPB, behavioral intention is the immediate antecedent of behavior, and intention is determined by three independent constructs:

1. **Attitude toward the behavior:** The degree to which a person has a favorable or unfavorable evaluation of the behavior
2. **Subjective norm:** The perceived social pressure to perform or not perform the behavior
3. **Perceived behavioral control:** The perceived ease or difficulty of performing the behavior, which also has a direct effect on behavior

TPB has been successfully applied in numerous studies predicting and changing alcohol-related behaviors among adolescents [16–18]. Interventions based on TPB have demonstrated effectiveness in reducing alcohol consumption intentions and behaviors in high-income countries [19, 20].

## ***Peer-led Educational Interventions***

Peer-led interventions leverage social influence processes that are particularly relevant during adolescence. Systematic reviews have shown that peer-led approaches can be effective in reducing substance use among young people [21, 22]. The advantages of peer-led interventions include enhanced credibility and relatability of messages, utilization of existing social networks, normalization of health-promoting behaviors, cost-effectiveness and sustainability, and empowerment of peer educators.

## ***Rationale for the Study***

Despite the growing burden of adolescent alcohol use in Ethiopia, as evidenced by national surveys showing that over one-third of youth consume alcohol [9], and the documented effectiveness of theory-based peer-led interventions in other settings, there is limited evidence from sub-Saharan Africa, particularly Ethiopia. Most existing studies in Ethiopia have focused on prevalence and associated factors, with few intervention studies [23, 24].

The Northeast Ethiopia region, specifically Dessie and Kombolcha towns, was selected because of high secondary school enrolment rates providing access to a large adolescent population; diverse socio-demographic characteristics representative of urban Ethiopia; limited

existing alcohol prevention programmes in schools; and reports of increasing alcohol availability and consumption among youth.

This study aims to address the evidence gap by developing and evaluating a culturally adapted, peer-led educational intervention grounded in the Theory of Planned Behavior to reduce alcohol use intentions and behaviors among secondary school students.

## ***Study Objectives***

This study aims to evaluate the effectiveness of a peer-led educational intervention based on the Theory of Planned Behavior (TPB) in reducing alcohol use intentions and self-reported alcohol use among secondary school students in Dessie and Kombolcha towns, Northeast Ethiopia.

## ***Study Hypotheses***

Post-intervention, intervention students will report:

1. More negative attitudes toward alcohol use
2. Stronger anti-alcohol subjective norms
3. Higher perceived behavioral control to resist alcohol
4. Lower intention to consume alcohol
5. Reduced self-reported alcohol use

## ***METHODS***

### ***Study Design and Setting***

A quasi-experimental pretest-posttest control group design with class-level allocation will be conducted from February to June 2021 in four public secondary schools in Dessie and Kombolcha towns, Northeast Ethiopia. This design was selected because individual-level randomization was not feasible due to the high risk of contamination within classrooms. Class-level allocation preserves the natural classroom environment, minimizes diffusion of intervention effects, and maintains logistical feasibility.

Dessie and Kombolcha towns are located in the South Wollo Zone of the Amhara National Regional State, approximately 400 kilometers northeast of Addis Ababa. The towns have a combined population of approximately 350,000 and serve as commercial and educational hubs

for the surrounding districts. The study will include public secondary schools offering grades 9-12.

This study protocol and the subsequent full report will adhere to the Transparent Reporting of Evaluations with Nonrandomized Designs (TREND) statement. A completed TREND checklist will be submitted as a supplementary file (S1 File) upon manuscript submission to ensure comprehensive and transparent reporting of all study elements,

### **Dates of Recruitment**

| Phase                    | Duration | Dates                      |
|--------------------------|----------|----------------------------|
| Baseline data collection | 1 week   | February 1-7, 2021         |
| Intervention delivery    | 4 weeks  | February 8 - March 7, 2021 |
| Follow-up period         | 3 months | March 8 - June 6, 2021     |
| Endline data collection  | 1 week   | June 7-15, 2021            |

### ***Participant Characteristics***

**Source Population:** All secondary school students enrolled in grades 9-12 in public secondary schools in Dessie and Kombolcha towns during the 2020/2021 academic year.

**Study Population:** Students aged 15-24 years enrolled in selected secondary schools who meet the eligibility criteria.

### **Inclusion and Exclusion Criteria**

| Inclusion Criteria                                                     | Exclusion Criteria                                                                        |
|------------------------------------------------------------------------|-------------------------------------------------------------------------------------------|
| Currently enrolled in grades 9-12 in selected public secondary schools | Unable to comprehend and complete the questionnaire due to cognitive or language barriers |

## Inclusion Criteria

Aged 15-24 years at the time of enrolment

Provide written informed consent (if  $\geq 18$  years) or parental consent and child assent (if 15-17 years).

Available for the duration of the study (February to June 2021)

## Exclusion Criteria

Planning to transfer to another school during the study period

Currently participating in another alcohol prevention programme

Severe mental or physical illness that would preclude participation

## *Sample Size Determination*

The sample size is calculated using the formula for comparing two proportions in cluster-based studies [24], accounting for the intra-cluster correlation coefficient (ICC). Assuming 80% power, 95% confidence level ( $\alpha = 0.05$ ), baseline prevalence of current alcohol use of 36.8% [9], and expected post-intervention prevalence of 26.8% (representing a 10% absolute reduction), the required sample size was determined. To account for clustering at the class level, an ICC of 0.02 was applied based on similar school-based studies [25], with an average cluster size of 30 students per class, yielding a design effect of 2. After adjusting for a 10% loss to follow-up, the total required sample was 1,496 students (748 per group).

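### The design effect of 2 does not follow from the stated ICC of 0.02 and 30 students per class, which give 1.58; the error is conservative, and the sample size paragraph should be corrected without changing enrolment

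*Protocol*

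**What the plan says.** All the planning inputs are in one paragraph of the protocol, under Sample Size Determination. It opens with "Assuming 80% power" at an alpha of 0.05, a "baseline prevalence of current alcohol use of 36.8" per cent, and an "expected post-intervention prevalence of 26.8% (representing a 10% absolute reduction" in percentage points).

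For clustering, it takes an ICC of 0.02 from the literature and then gives the class size and the result together: "with an average cluster size of 30 students per class, yielding a design effect of 2". Once a 10% allowance for dropout has been made, it concludes that "the total required sample was 1,496 students (748 per group").

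The Intervention Overview table agrees on class size: 30 students per group in 25 groups, which is 750 students and so matches the 748 in the intervention arm. Neither place mentions rounding, a safety margin, unequal class sizes or a higher planning ICC as the source of the 2.

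**The concern.** The paragraph presents 2 as the result of the ICC and class size printed just before it, and it is not that result. The figure then multiplies straight into the required sample size, so the error carries through to a number on which the trial rests.

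What is at stake is whether the plan can be read, not whether the trial is adequate. If the ICC of 0.02 is the planning value, the trial has more power than stated and asks about 300 more students to take part than the stated assumptions require. If 2 is the planning value, the printed ICC and class size are not the basis for the sample size, and the apparent spare power does not exist. The text does not allow a reader to tell these apart.

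**Working it through.** **Inputs** (all from Sample Size Determination): p1 = 0.368, p2 = 0.268, power 80%, alpha 0.05, ICC 0.02, class size m = 30, loss 10%. Sidedness is not stated. I assume a two-sided test, which is the version that reproduces the plan's figure (z values 1.960 and 0.842).

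**1. The plan's own figure, taking 2 as given.** Two ordinary routes reach 748 per group:

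- Unpooled variance, dividing by retention: n = (1.960 + 0.842)² × (0.368 × 0.632 + 0.268 × 0.732) / 0.10² = 336.5; 336.5 × 2 / 0.90 = 747.8, so 748.
- Pooled variance, inflating by 10%: n = 339.3, rounded up to 340; 340 × 2 × 1.10 = 748.

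The protocol does not show which was used, and it does not matter here. Both routes need the multiplier 2.

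**2. The design effect from the stated inputs.** 1 + (m − 1) × ICC = 1 + 29 × 0.02 = 1.58.

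**3. What a design effect of 2 would need.**

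- At m = 30: ICC = (2 − 1) / 29 = 0.0345.
- At ICC = 0.02: m = 1 + (2 − 1) / 0.02 = 51 students per class.
- From unequal class sizes alone, using 1 + ((1 + CV²)m − 1) × ICC: (1 + CV²) × 30 = 51, so CV² = 0.70 and CV is about 0.84.

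**4. Sample size with 1.58.**

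| Route | Per group | Total |
|---|---|---|
| 336.5 × 1.58 / 0.90 | 590.8, so 591 | 1,182 |
| 340 × 1.58 × 1.10 | 590.9, so 591 | 1,182 |
| 340 × 1.58 / 0.90 | 596.9, so 597 | 1,194 |

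The planned 1,496 exceeds these by 302 to 314 students: 1,496 / 1,194 = 1.25 and 1,496 / 1,182 = 1.27, so it is 25% to 27% larger.

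**5. Power at 1,496.** Analysed per group: 748 × 0.90 = 673.2. Power = Φ(0.10 / √(0.42875 × DE / 673.2) − 1.960), where 0.42875 is the sum of the two binomial variances.

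| Design effect | Effective n per group | Power (unpooled) | Power (pooled) |
|---|---|---|---|
| 1.58 | 673.2 / 1.58 = 426.1 | 88.3% | 88.1% |
| 2 | 673.2 / 2 = 336.6 | 80.0% | 79.7% |

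If class size is also reduced by the 10% loss, to 27, the design effect is 1 + 26 × 0.02 = 1.52 and power is about 89%. The conclusion does not change.

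**The case against.** The strongest reply is that nothing is lost. The error is in the safe direction. Once 2 is accepted the rest of the arithmetic is sound, and a planner may well have rounded up or taken 2 as a margin against a higher ICC or uneven classes. The first two parts stand in full: only the step from ICC and class size to design effect fails. The third is possible, but the protocol does not say it; the text derives 2 from the stated inputs. A deliberate margin is a legitimate answer, but it has to be written down.

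Three stronger readings are tempting, and the protocol does not support them.

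- *A reader might infer that the trial is underpowered.* It is not, for the stated effect: power is about 88% at a design effect of 1.58 and about 80% at 2.
- *A reader might infer that the true planning ICC must have been about 0.034.* That is one way to reach 2. Larger classes, unequal classes or a plain margin are others, and the text does not decide between them.
- *A reader might infer that the 36.8% starting prevalence is also an error,* because under Alcohol Use in Ethiopia the protocol cites a review that "estimated the prevalence of current alcohol consumption among school adolescents and youths in Ethiopia at 27" per cent, close to the 26.8% target. This is a matter of judgement. The 36.8% is past-month use at ages 15–24, which matches the eligible ages and the 30-day outcome. The 27% is reported with marked regional variation, and no figure is given for the two study towns. Nor does it weaken the plan for the effect it states: a 10-point drop from 27% to 17%, with 673 analysed per group, has about 94% power at 1.58 and 88% at 2. Lower values (about 72% and 62%) appear only if the reduction is assumed to be relative, 10 / 36.8 = 27%, so from 27.0% to 19.7%. The protocol plans an absolute reduction; the relative one is an assumption from outside the plan.

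**Conclusion.** The contradiction is certain and confined to one step. The stated ICC and class size give a design effect of 1.58, not 2. On those inputs the required total is about 1,182 to 1,194 rather than 1,496, and the power at 1,496 with 10% loss is about 88% rather than 80%. If 2 is kept as the planning value, 1,496 and about 80% power are right, but then the sentence deriving it is wrong.

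The figures assume a two-sided 5% test, the normal approximation for two proportions, equal class sizes and exactly 10% loss. The choice of variance formula and loss adjustment moves the total by about a dozen students and the power by well under one percentage point. The error is conservative, so this should be fixed for accuracy and is not a reason to doubt that the trial can detect its stated effect.

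**What to change.** Rewrite the clustering and sample size sentences in one of two ways, leaving enrolment at 1,496:

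- **Keep the ICC of 0.02 and 30 per class.** State the design effect as 1.58, note that about 1,182 to 1,194 students would give 80% power, and state power of about 88% at 1,496 with 10% loss.
- **Keep the design effect of 2.** Say that it was chosen as a planning value and why: a margin, unequal class sizes, or an ICC of about 0.034 at 30 per class. Remove the wording that derives it from 0.02 and 30, and keep the power at about 80%. If unequal class sizes are the only reason, give the variation assumed, since that reason alone needs a CV of about 0.84.

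In either case, show the base sample size per group and the way the 10% loss was applied, so that 748 can be reproduced.

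Optionally, add a sensitivity figure at the 27% student prevalence: the drop detectable with 80% power is about 8.0 points at a design effect of 1.58 and 9.0 points at 2. If power for a constant relative reduction is quoted as well, label it as an added assumption.

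The cost is one reworded paragraph, with no extra students and no change to the design.

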## *Sampling and Allocation Procedure*

**School Selection:** From the six eligible public secondary schools in Dessie and Kombolcha towns, four schools will be randomly selected using a computer-generated random number sequence. Two schools will be selected from Dessie and two from Kombolcha to ensure geographic representation.

**Class Selection and Allocation:** Within each selected school, classes in grades 9-12 will be stratified by grade level. From each grade, classes will be randomly assigned to either intervention or control arms using a computer-generated random sequence prepared by an independent researcher not involved in data collection. The allocation sequence will be generated prior to recruitment, and allocation concealment will be maintained by using

sequentially numbered, opaque, sealed envelopes to prevent selection bias. All students in selected classes will be invited to participate.

**Allocation Ratio:** 1:1 (intervention: control)

**Rationale for Class-Level Allocation:** This approach minimizes contamination between intervention and control participants, maintains logistical feasibility, and preserves the natural classroom environment.

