### Covariates

| Domain         | Variables                                                                                                                                                                                                         |
|----------------|-------------------------------------------------------------------------------------------------------------------------------------------------------------------------------------------------------------------|
| Demographics   | Age (years, categorized as 15-19, 20-24), Sex (male, female), Grade level (9-10 lower secondary, 11-12 upper secondary), Religion (Orthodox, Muslim, Protestant, Other), Ethnicity (Amhara, Oromo, Tigray, Other) |
| Socioeconomic  | Father's education (no formal, primary, secondary, or higher); Mother's education (no formal, primary, secondary, or higher)                                                                                      |
| Family Factors | Family discussion about alcohol (yes/no), parental alcohol use (yes/no)                                                                                                                                           |
| Peer Factors   | Peer alcohol use (yes/no)                                                                                                                                                                                         |

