### ***Baseline Comparability:***

| Variable Type                                                                                   | Test                 |
|-------------------------------------------------------------------------------------------------|----------------------|
| Categorical variables                                                                           | Chi-square tests     |
| Continuous variables (normal distribution)                                                      | Independent t-tests  |
| Continuous variables (non-normal distribution)                                                  | Mann-Whitney U tests |
| Variables with $p < 0.05$ will be considered unbalanced and adjusted in multivariable analyses. |                      |
| Within-Group Changes:                                                                    |                      |

| Outcome Type | Test            | Effect Size |
|--------------|-----------------|-------------|
| Continuous   | Paired t-tests  | Cohen's d   |
| Dichotomous  | McNemar's tests | Odds ratios |

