### **Between-Group Comparisons:**

| Outcome Type | Test                | Effect Size             |
|--------------|---------------------|-------------------------|
| Continuous   | Independent t-tests | Cohen's d with 95% CI   |
| Dichotomous  | Chi-square tests    | Odds ratios with 95% CI |

**Generalized Estimating Equations (GEE)** will be used to account for clustering at the class level:

| Component             | Specification                                                     |
|-----------------------|-------------------------------------------------------------------|
| Distribution family   | Normal for continuous outcomes; binomial for dichotomous outcomes |
| Link function         | Identity for continuous; logit for dichotomous                    |
| Correlation structure | Exchangeable (assumes equal correlation within clusters)          |

| Component | Specification |
|-----------|---------------|
|-----------|---------------|

|                 |             |
|-----------------|-------------|
| Clustering unit | Class level |
|-----------------|-------------|

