**Adjusted Variables:**

- Baseline value of outcome variable
- Father's education
- Mother's education
- Family discussion about alcohol
- Baseline alcohol use status

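### Classes are randomised within school and grade but the GEE adjusts for neither, so its standard error is somewhat too wide if outcomes differ between schools or grades

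*Protocol*

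**What the plan says.** Under Sampling and Allocation Procedure, "four schools will be randomly selected using a computer-generated random number sequence", two in each town. Then: "Within each selected school, classes in grades 9-12 will be stratified by grade level". And: "From each grade, classes will be randomly assigned to either intervention or control arms using a computer-generated random sequence". The overall ratio is 1:1. The strata are therefore school by grade, 4 x 4 = 16.

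Under Between-Group Comparisons, GEE "will be used to account for clustering at the class level", with exchangeable correlation. The Adjusted Variables list opens with "Baseline value of outcome variable" and adds both parents' education, whether the family talks about alcohol, and drinking status at baseline. School and grade are not on it.

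The Covariates table holds "Grade level (9-10 lower secondary, 11-12 upper secondary", which is coarser than the four grades used for allocation. School is not in that table.

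The only other way into the model is the rule under Baseline Comparability: variables with p < 0.05 "will be considered unbalanced and adjusted in multivariable analyses".

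**The concern.** When allocation is stratified, differences between strata fall about equally on both arms and drop out of the true sampling error of the treatment effect. A model without the strata still sees those differences as variation between classes, and the robust class-level standard error includes them. The reported standard error then exceeds the true one.

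The imbalance rule is unlikely to repair this. It selects variables that differ between arms at baseline, and school and grade are the two that the allocation is built to balance.

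At stake is precision on both primary outcomes: confidence intervals wider than they need be, and a test that rejects less often than its nominal level. The Protocol names its model and covariates in its own analysis section, so this is a stated choice and not a detail left for later.

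**Working it through.** **Inputs from the Protocol**
- Sample Size Determination: 36.8% versus 26.8%, 80% power, alpha 0.05 (taken as two-sided), ICC 0.02, 30 students per class, stated design effect 2, 10% loss, 748 per arm.
- Intervention Overview: 25 intervention groups of 30, so about 50 classes in all (1,496 / 30 = 49.9).

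**The plan's own figure.** The two-proportion formula (pooled, no continuity correction) gives 340 per arm. 340 x 2 x 1.10 = 748 per arm, or 1,496. It reproduces.

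**Assumption.** Let f be the share of between-class variance due to school and grade. The Protocol does not give f, so it is varied from 0 to 0.75. Arms are assumed balanced within strata, and baseline adjustment is ignored at this step.

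**Formulas**
- Analysed per arm: n = 748 x 0.9 = 673. Mean rate p = (0.368 + 0.268) / 2 = 0.318.
- SE = sqrt(2p(1-p)/n x DE) = 0.0254 x sqrt(DE).
- Reported without strata: DE = 1 + 29 x 0.02 = 1.58, so SE = 0.0319.
- True SE, and SE with strata in the model: DE = 1 + 29 x 0.02 x (1-f).
- Power without strata = Phi((0.10 - 1.96 x SE reported) / SE true). Power with strata = Phi(0.10 / SE true - 1.96).
- Type I error without strata = 2 x (1 - Phi(1.96 x SE reported / SE true)).

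Worked for f = 0.50: the true DE is 1.29 and the true SE 0.0288. The SE ratio is sqrt(1.58/1.29) = 1.107. Power is Phi(1.30) = 90.3% without strata and Phi(1.51) = 93.4% with them.

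| f | True DE | SE ratio | Type I error without strata | Power without / with strata |
|---|---|---|---|---|
| 0 | 1.58 | 1.000 | 5.0% | 88.0% / 88.0% |
| 0.25 | 1.44 | 1.049 | 4.0% | 89.1% / 90.8% |
| 0.50 | 1.29 | 1.107 | 3.0% | 90.3% / 93.4% |
| 0.75 | 1.15 | 1.175 | 2.1% | 91.6% / 95.7% |

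The loss is about 2 to 4 points. As a sensitivity check, the stated design effect of 2 corresponds to an ICC of 1/29 = 0.0345. There, power without / with strata is 81.1% / 84.6%, 83.0% / 89.6% and 85.2% / 94.1% for f = 0.25, 0.50 and 0.75, again before baseline adjustment.

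**With the planned baseline adjustment.** A simulation used 50 classes of 27, a within-stratum ICC of 0.02, a 10-point effect and 1,500 runs. It assumed baseline-endline correlations of 0.3, 0.5 and 0.7, which the Protocol does not give.
- Prevalence rising from 30% to 44% over grades: adding strata gains 1.4, 0.8 and 0 power points.
- Prevalence rising from 25% to 50%: gains of 6.3, 2.2 and 0.3 points, and power without strata of 91%, 97% and 99.6%.

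These gains are upper bounds, because the strata model was run with an uncorrected sandwich that rejected 7-9% under the null. A second simulation (1,200 runs, corrected variance, correlation 0.5) put the remaining loss at about 0.5 to 2 points.

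**Check on the remedy.** In a partial run (48 classes, 400 runs per setting), GEE with school and grade and an uncorrected sandwich rejected 6.5% to 11.5% under the null. In a 4,000-run simulation the uncorrected test with strata rejected 8-9%, and the corrected one with a t reference 5-6%.

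**The case against.** The strongest reply is that the plan already adjusts for the baseline outcome and baseline drinking. A grade or school gradient would be present at baseline too, so most of the excess is absorbed. This stands, and it keeps the point small.

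A reader might infer a much larger loss. Simulated without baseline adjustment, with prevalence rising from 25% to 50% over grades, the standard error is about 27% too wide and power is 79% instead of 91%. The documents do not support those figures as a description of this trial. They omit an adjustment that the plan fixes. They also lay the gradient on top of a within-stratum ICC of 0.02, which takes the total ICC to about 0.057 (about 0.032 for the 30-44% gradient) against the planned 0.02. No prevalence by school or grade is given anywhere in the Protocol.

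Two further replies stand in part. The Protocol does not say that the 1:1 ratio holds within each stratum; where it does not, stratification balances less and the excess shrinks. And the remedy can do harm: added with ordinary robust standard errors, it turns a mildly conservative test into a liberal one. That argues for pairing it with a variance correction, not for leaving the strata out.

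**Conclusion.** The point holds as a conditional loss of efficiency. The allocation uses school and grade, the stated model uses neither, and the imbalance rule is unlikely to bring them in. At a total ICC of 0.02 the cost before baseline adjustment is a standard error about 5-17% too wide and 2-4 power points, if school and grade carry 25-75% of between-class variance. After the planned baseline adjustment, 0-2 points is typical; about 6 needs both a steep gradient and a weak baseline-endline correlation. With no gradient there is no loss. The direction is certain; the size rests on assumed gradients and correlations. The power figures are for current alcohol use; for intention only the direction is claimed.

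A reader might also infer bias, inflated type I error or an underpowered trial. The omission produces neither of the first two. At the planned ICC, power stays at or above 88% in the table with or without the strata. The type I figures there are large-sample values; with about 50 classes an uncorrected sandwich can be somewhat liberal in its own right, which is a separate matter from the missing strata.

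**What to change.** Add school (four levels) and grade as allocated (9, 10, 11, 12) as fixed effects to the GEE for every outcome, and keep grade in four levels in the analysis data. In the same amendment, require a small-sample-corrected robust variance and a t reference with degrees of freedom equal to classes minus parameters. With intercept, arm and six stratum terms that is 50 - 8 = 42; state whether the student-level covariates are also counted. The two changes should be adopted together or not at all.

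The cost is 3 + 3 = 6 class-level parameters and revised analysis wording, with no change to the 1,496 students. School is not in the Covariates table but must be known to carry out the allocation, so it should be listed and kept in the dataset. The Software section names only SPSS 25 for analysis. Confirm that it can produce the corrected variance, or name software that can.
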